**Figure 1 F1:**
[figure not shown]
**Flow chart of participants**. AD: anti-depressives; CES-D: Center for Epidemiologic Studies Depression scale; PAID: Problem Areas In Diabetes scale; ADSCI: Diabetes Self-care Inventory; SF-12: Short-Form-12; EQ-5D: Euroqol 5D; CBT: Cognitive behavioural therapy.

### Study procedures

The recruitment and screening procedure has been developed, so that patients interested in joining the study can visit the research website. There, the patient will be invited to read the study information and provide written informed consent. After receipt of the consent form, the patient will receive a password per e-mail allowing him/her to log in and complete the online screening questions. For the baseline measurement, patients are invited to fill out a booklet of questionnaires on the Internet, -which will take approximately 30 minutes-containing demographic data, in – and exclusion criteria, and depressive symptoms (Center for Epidemiological Studies Depression scale (CES-D) >16) [22]. If a patient does not qualify, this is explained and the patient is advised to contact his/her GP for further advice. If eligible, the patient will be interviewed by telephone using the Composite International Diagnostic Interview (CIDI). Data from this CIDI interview will be used to specify type of mood disorder (DSM-IV). Those with bipolar disorder, depression with psychotic features and patients who suffer from current suicidal ideation will be excluded. After eligibility is confirmed the patient is enrolled in the study.

### Treatment allocation

Randomisation by computer will assign individual patients to either the experimental or control condition.

### Recruitment

The on-line depression course will be delivered through a website. The study will be advertised in the Netherlands and Flanders (Dutch speaking part of Belgium) in clinics (e.g. hospitals, GP's, pharmacy's, rehabilitation centres) and through various media (e.g. patient journals, specialist journals, websites, e-mails, flyers, newspapers etc.). It will be advertised as a web-based course for persons with diabetes (type 1 or type 2) to help improve a depressed mood. Patient information on the study will be available on the research website. Inclusion and exclusion criteria will be stated clearly on this website.

### Study population

The source population consists of adult diabetes patients with co-morbid depression. Blinding of subjects will -due to ethical reasons- not be carried out.

Inclusion criteria are: ≥18 years of age; having type 1 or type 2 diabetes (diagnosed > 3 months prior to study by a physician); having a depressed mood, as indicated by a score of 16 or higher on the Center for Epidemiological Studies Depression scale (CES-D); depression diagnosed by the CIDI-interview; having access to the Internet at home and having an e-mail address.

Exclusion criteria are: not having easy access to the Internet, reading problems (e.g. due to insufficient Dutch language skills, visual impairments or illiteracy); currently taking anti-depressant medication; a history of suicide attempt(s); current suicidal ideation (measured with the CIDI); bipolar disorder (CIDI); co-morbid organic psychiatric disorder (CIDI); loss of significant other < previous 6 months; or pregnancy.

### Description of interventions

#### Intervention group

Patient enrolment will occur individually on a continuous basis, i.e. at any point in time during the study period. The number of included participants is not limited by physical capacity other than the number of coaches available. After inclusion criteria are met and the patient has returned the informed consent s/he will be randomly assigned to the intervention or the control group.

Patients assigned to the intervention group will receive a password per e-mail with which they can log in to the course. They will be instructed (and reminded per e-mail) to complete one session per week, during 8 consecutive weeks.

Coaches will send e-mails to participants as a way to encourage them to continue their efforts. Such reinforcement should help to keep patients on track with the course and lower the risk of drop-out. They also provide the participants with feedback on their homework assignments. It is clearly stated that coaches will not give advice on personal issues.

#### Control group

Control group patients will receive an e-mail in which they are informed of the randomisation result, which means they will start the course after 12 weeks. To reduce the risk of loss of interest; participants placed on the waiting-list will automatically receive weekly protocollised e-mails with motivating, positive feedback to enforce them to remain involved in the study.

After eight weeks they are invited per e-mail to fill in the questionnaires again. Twelve weeks after randomization patients will undergo a second screening (using the CES-D-score ≥ 16 as a first screener for depression and additionally the CIDI interview) to confirm depression. If still eligible, the patient is invited to follow the course. Patients, who do not qualify, i.e. show (spontaneous) remission, are excluded at this point. Patients who developed suicidal ideation during the 12 weeks waiting period, are offered the opportunity to have an appointment with a diabetes psychologist of the VU University Medical Centre or a colleague nearby in case the distance from the participant's home to the VUMC should be problematic.

The effectiveness of the intervention is determined directly after completing the web-based intervention up till 6 months follow-up (see Consort flow chart in Figure 1).

If the depression has deteriorated at the end of the course, as indicated by the scores of the CES-D, a consultation with a diabetes psychologist at the VU Medical Centre is offered to the patient. In agreement with their General Practitioner a decision will be made about further treatment or hospitalization.

### Intervention development and trial design

The Dutch version of the manual-based self-help course named 'Coping with Depression' ('In de put, uit de put') has been adapted as web-based intervention ('Kleur je Leven') [23,24]. This intervention has been adjusted further by our team to fit the needs of patients with diabetes ('Diabetergestemd'). Based on our research, clinical experience and input from an expert panel of diabetes patients, the following topics were incorporated: managing 'poor' test results, uncertainty about blood glucose fluctuations and negative emotions, communication with health care professionals, talking about diabetes with others, the burden of daily self-management, and coping with diabetes-related worries (e.g. about hypoglycaemia and late complications). The course consists of 8 consecutive weekly lessons. The course will provide information, practice examples, exercises/self-tests and homework assignments. The web-based course is delivered on an individual basis. Patients weekly receive (protocollized) feedback on their homework assignments from their coaches by e-mail. The coaches are psychologists and residents in clinical psychology from the department of Medical Psychology of the VU medical centre, supervised by the research team. An internet-based group forum, which will be moderated by our team, is offered to participants to give them the opportunity to share experiences, provide support and discuss issues related to depression and diabetes [25]. In the forum, specific treatment issues (e.g. related to oral medication or insulin) may not apply to all participants, but this should not be problematic. Rather, the mix of disease types and experiences can serve to illustrate the common features of diabetes and depression (thoughts, emotions and behaviors), while respecting individual differences.

It will be clearly stated that during the course of the study, all participants are allowed to make use of additional mental health care services if they feel a need to do so.

### Outcome Assessment

#### Primary outcome measures

Primary outcome measure is the level of depression, measured by the online administered self-reported depression questionnaire Center for Epidemiological Studies Depression scale (CES-D) [26] at baseline, directly after completion of the course and at one and six months follow-up.

#### Secondary outcome measures

Secondary outcome measures are: diabetes-specific emotional distress (PAID) [27], satisfaction with the course (self-developed questions), perceived health status (EQ5D and SF-12) [28], diabetes self-care behaviours (Amsterdam Diabetes Self Care Inventory), self-reported episodes of hypoglycaemia and glycaemic control (HbA_1c_) retrieved from the patients' medical charts via their physician.

#### Covariates

Additionally, information on potentially confounding factors and effect modifiers will be collected by means of self-report: socio-demographic data (age, gender, marital status, highest level of completed education, and current occupation), lifestyle issues (smoking, body mass index (BMI), substance/alcohol abuse), data on diabetes (type of diabetes, duration, treatment regimen, co-morbidity) and additional mental health care consumption.

### Statistical Analyses

Analyses will be conducted according to the intention to treat principle. The data will be presented as categorical and continuous variables. Baseline characteristics will be compared for the intervention and waiting-list group using Student *t*-tests and χ^2^-tests. Analysis of variance (ANOVA) will be conducted with the CES-D (depression) as dependent variable, with two independent variables: time (within-subject) and group (between-subject). The same analysis will be performed with the PAID score (diabetes-related emotional distress) as dependent variable. Two analyses will be conducted. Firstly, the direct effect of the intervention will be determined. ANCOVA's will be performed in order to test whether both groups have different scores on the CES-D, at different points in time, with correction for potential confounders at baseline. Secondly, pre-post measurements will be conducted of all participants who have received the intervention. This will be analysed by means of a longitudinal regression analysis, which will be performed using Generalized Estimating Equations (GEE) [29], taking into account the correlational nature of repeated measures data within subjects, and securing minimal loss of patients due to incomplete data. Clinical effectiveness will be calculated by the amount of people who after completion of the course have a score on the CES-D of <16. The effect size will be calculated using Cohen's *d *[30].

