### Power calculation

The sample size was calculated using STATA, based on clinically relevant differences. Effect Sizes (ES) are calculated as the difference between the control group and the intervention group after the intervention, divided by the pooled standard deviation [30]. With 100/100 patients the study is powered to detect an ES of 0.35 (one-sided), with a power of 80% (α = 0.05). Based on a meta-analysis [23], we may expect an ES of 0.5 to 0.6 [18]. We anticipate 30% non-completion/exclusion, which will be compensated by over sampling (n = 286; 143 in each group).

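### The pooled pre-post analysis has no control and starts from CES-D scores selected at the entry cut-off, so it can describe change after the course but cannot show effectiveness

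*Protocol article*

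**What the plan says.** Four parts of the protocol article bear on this point.

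- **Selection and baseline.** Study population requires "having a depressed mood, as indicated by a score of 16 or higher on the Center for Epidemiological Studies Depression scale (CES-D", together with a depression diagnosis from the CIDI. Study procedures places the CES-D screen inside the baseline booklet: "For the baseline measurement, patients are invited to fill out a booklet of questionnaires on the Internet". The CES-D is also the primary outcome (Primary outcome measures).
- **Wait-list patients.** Under Control group, they are screened again at week 12 with the same CES-D cut-off and the CIDI. "If still eligible, the patient is invited to follow the course"; those in remission are excluded at that point.
- **Analyses.** Statistical Analyses names two. The first is the randomised one, an ANCOVA comparing the arms. Then: "Secondly, pre-post measurements will be conducted of all participants who have received the intervention", by GEE. Clinical effectiveness is the number scoring below 16 after the course, which is the entry cut-off again.
- **Time span of the claim.** Control group states: "The effectiveness of the intervention is determined directly after completing the web-based intervention up till 6 months follow-up". Strengths and Limitations says the trial is powered for conclusions about effectiveness at 6 months. Controls may start the course 12 weeks after randomisation.

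**The concern.** Patients admitted because a fluctuating self-report was high on one occasion will, on average, score lower the next time without any treatment. Here the selecting score is itself the pre value for the intervention arm. For wait-list patients the protocol does not say whether pre means the original baseline or week 12, but both were selected at the same cut-off. A randomised comparison removes the artefact because both arms share it. A pre-post model in treated patients does not, and GEE deals only with within-patient correlation and incomplete data.

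The pooled set also mixes patients selected once with patients selected twice, because remitters are removed from the wait-list contribution only. By excluding them, the protocol itself allows for improvement without treatment.

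What is at stake is the claim beyond week 12. Once controls can start the course, no untreated comparator remains, so only uncontrolled change could support a statement about effectiveness at 6 months.

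**Working it through.** **The plan's own figure.** The design states "With 100/100 patients the study is powered to detect an ES of 0.35 (one-sided), with a power of 80% (α = 0.05"). The usual formula gives n = 2(1.645 + 0.842)² / 0.35² ≈ 100.9, so 101 per arm; with 100 per arm the power is 79.7%. Then 100 / 0.70 = 142.9, so 143 per arm, which agrees with "We anticipate 30% non-completion/exclusion, which will be compensated by over sampling (n = 286; 143 in each group"). The 0.35 is therefore reproduced, as a one-sided, between-group effect.

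**Inputs for the artefact.** The cut-off of 16 is from Study population (Study procedures writes it as above 16; the two should be reconciled). The rest is assumed, since the protocol gives no figures: SD 10, applicant mean 20, 24 or 28, retest correlation r from 0.5 to 0.8, normal scores, no course effect and no natural remission.

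**Formulas.** With c = (16 − mean)/SD and λ = φ(c)/(1 − Φ(c)):

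- expected untreated fall = (1 − r) × SD × λ
- variance of selected pre scores = SD² × v, where v = 1 − λ(λ − c)
- variance at the next measurement = SD² × (r²v + 1 − r²)
- d = fall / pooled SD of the two measurements

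**Upper end (mean 20, r 0.5).** c = −0.4 and λ = 0.562. The fall is 0.5 × 10 × 0.562 = 2.81 points. The SDs are 6.78 and 9.30, pooled 8.14. So d = 2.81 / 8.14 = 0.345.

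**Lower end (mean 28, r 0.8).** c = −1.2 and λ = 0.219. The fall is 0.2 × 10 × 0.219 = 0.44 points. The pooled SD is 8.63. So d = 0.05.

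**Effect of the CIDI.** Entry also needs a CIDI diagnosis, which weakens selection on the CES-D score itself. I simulated it (2 million draws) as an independent measure of equal reliability with the same cut, which is a further assumption.

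| Applicant mean | d, CES-D selection only (r 0.8 to 0.5) | d, with CIDI gate (r 0.8 to 0.5) |
|---|---|---|
| 20 | 0.15 to 0.345 | 0.10 to 0.27 |
| 24 | 0.09 to 0.21 | 0.06 to 0.17 |
| 28 | 0.05 to 0.12 | 0.04 to 0.10 |

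**Wait-list patients.** Under CES-D selection only, those re-selected at week 12 fall by a further 0.30 to 2.15 points from their week-12 score without treatment. From week 8, which selects nobody, the simulated fall is 0.00; but a real week-8 starting point leaves four untreated weeks inside the change.

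**Proportion below 16.** Under CES-D selection only, 5 to 23% of untreated patients would score below 16 at the next measurement.

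**Would it look significant?** For a paired contrast with pre/post correlation ρ, dz = d/√(2(1 − ρ)), and the chance of two-sided significance is Φ(dz√n − 1.96). With d = 0.20 and ρ from 0.5 to 0.6, this is 52% for n = 100 (ρ 0.5) and 88% for n = 200 (ρ 0.6).

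**Randomised contrast.** With no course effect, r = 0.6 and the applicant mean 0.5 SD above the cut, the simulated between-arm d is 0.00, while the pre-post d is 0.25 (0.19 with the gate).

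**The case against.** The strongest reply is that the protocol already determines the direct effect by the randomised ANCOVA and lists the pre-post GEE second, with no hypothesis attached. The stated aim is comparative. How a secondary analysis is labelled is often left to an analysis plan. Much of this stands: the primary inference is sound.

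Three stronger readings are tempting, and the document does not support them.

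- A reader might infer that the Control group section commits to judging effectiveness by pre-post change. It says only when effectiveness is determined and names no contrast.
- A reader might infer that a pre-post Cohen's d will be reported and can be set against 0.35. Power calculation defines the effect size as "the difference between the control group and the intervention group after the intervention, divided by the pooled standard deviation", so the two can be compared in magnitude only.
- A reader might infer that the artefact is about as large as the design effect. Within the assumed range, that happens only at the lowest applicant mean and lowest correlation, and only if the CIDI does not weaken the selection. With the gate modelled, the maximum is 0.27 and most settings are well below it.

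What the reply does not answer is the time span. The protocol states conclusions on effectiveness up to 6 months, and after week 12 it has only uncontrolled change with which to support them.

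**Conclusion.** The point holds in limited form. The pooled pre-post GEE cannot separate the course from regression to the mean and natural remission, nor can the proportion below 16 if it is counted in treated patients only.

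The size is unknown. Under the assumptions above, regression to the mean alone gives a pre-post d of about 0.05 to 0.345, or 0.04 to 0.27 with the CIDI gate. Natural remission would add to this by an amount for which the protocol gives no figure. An artefact in the middle of the range could still be statistically significant at the planned numbers.

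This is worth correcting because it decides which conclusions the trial can draw after week 12. It does not threaten the randomised result.

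**What to change.** - State in Control group, Statistical Analyses, and Strengths and Limitations that effectiveness is concluded only from the between-arm comparison before controls start the course, at 8 and 12 weeks.
- Report the pooled pre-post GEE and the later follow-ups as descriptive data on maintenance, without an efficacy claim or effect size.
- Show beside them the untreated change from baseline to weeks 8 and 12 in all randomised controls, including those who do not go on to the course.
- Compare the proportion with CES-D below 16 between arms.
- If wait-list patients enter the pre-post model, show their change from both week 8 and week 12. Week 12 is a selected score, and week 8 includes four untreated weeks; neither is clean alone.

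The cost is rewording in three sections and a few added summaries from measurements already scheduled. The real downside is that the pooled and 6-month results can no longer support an efficacy statement.

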Although web-based administration of questionnaires is widely used, we should remind ourselves that the psychometric properties of internet-administered questionnaires may not be equal to those of paper-and-pencil versions [32]. On the other hand, in an earlier study we have found that the paper-and-pencil and the computerised versions of a short psychological well-being questionnaire appeared to be equivalent [33]. The major difference appears to be that respondents are more honest and revealing when filling out via the Internet, resulting in a relatively higher reported level of symptomatology. We have therefore chosen to confirm or decline the diagnosis of depression by a telephone administered diagnostic interview (CIDI). Our study will show if such diagnostic procedure is required in future projects applying W-CBT in order to reduce the risk of 'false positives'.

Also the psychometric properties of the following on-line questionnaires will be examined and compared to the paper-and-pencil versions: the PAID, SF-12 and the ADSCI.

We hypothesise that improved mood will be associated with improved diabetes self-management and we will test whether W-CBT has favourable effects on self-reported diabetes self-care behaviours, using the Amsterdam Diabetes Self-care Inventory (ADSCI) that was developed by our team and used in previous trials [12,13,34]. The psychometric properties of the Amsterdam Diabetes Self Care Inventory (ADSCI) have not yet been published, but a report on the validity and reliability of the scale is planned based on data on file.

Ethical and practical considerations have led us to decide that all participants are allowed to use additional mental health care (MHC) services during the trial. Usage of additional services therefore is a potential confounder that will be measured and taken into account in the statistical analyses.

Drop-out is often a problem in web-based therapy trials. In adapting the generic coping with depression course to the needs of people with diabetes, we expect to reduce drop-out. In an attempt to further reduce the attrition rate, support e-mails will be send out to participants by their coach, to encourage them to stay involved in the course. Likewise, those in the waiting list condition will receive e-mails aimed to maintain contact and encourage them to participate.

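### The pre-post CES-D analysis uses ordinary GEE, which keeps incomplete records but does not in general protect against drop-out that depends on earlier scores

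*Protocol article*

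**What the plan says.** The Statistical Analyses section of the protocol article describes two analyses.

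- **Between groups.** The direct effect is tested on the randomised arms: "ANCOVA's will be performed in order to test whether both groups have different scores on the CES-D". A time-by-group ANOVA is also described.
- **Pre-post.** In the second analysis, "pre-post measurements will be conducted of all participants who have received the intervention". This is a longitudinal regression by GEE. Two reasons are given: it allows for within-subject correlation, and it helps in "securing minimal loss of patients due to incomplete data". No weighting or imputation is mentioned, so I read it as ordinary, unweighted GEE.

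Under Primary outcome measures, the CES-D is taken at baseline, directly after the course, and at one and six months.

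On losses, the Power calculation says "We anticipate 30% non-completion/exclusion", and Strengths and Limitations says "Drop-out is often a problem in web-based therapy trials". Neither place says who is expected to drop out, or how many CES-D scores will be missing.

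**The concern.** Keeping a patient's available visits is one thing. Estimating the mean that would have been seen had nobody left is another. Unweighted GEE is guaranteed consistent in general only if missingness is unrelated to the outcomes, given the covariates in the model. A likelihood-based model with a correct covariance uses the same records and also stays valid when drop-out depends on scores already observed.

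This matters for the size of the 6-month change. Controls who are still eligible are invited to the course 12 weeks after randomisation, so the later follow-up rests largely on the pre-post analysis. That analysis has no concurrent control, so any bias from selective drop-out passes straight into the reported change.

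**Working it through.** **1. The plan's own figures.** The article gives no figure for the GEE analysis, only a sample size. For ES 0.35, one-sided α = 0.05 and 80% power:

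n per arm = 2 × (1.645 + 0.842)² / 0.35² ≈ 101, against the stated 100. Power at 100 per arm is 79.7%. Inflation gives 100 / 0.70 = 142.9, so 143 per arm and 286 in all.

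The figures reproduce. The 30% is therefore treated as patients who contribute nothing to the comparison, but it is a combined figure for non-completion and exclusion.

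**2. Why the working correlation matters.** With an identity link, the GEE estimate solves

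β̂ = (Σ Xᵢ′Vᵢ⁻¹Xᵢ)⁻¹ Σ Xᵢ′Vᵢ⁻¹yᵢ,

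summed over the observed visits of each patient.

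- *Independence* (Vᵢ diagonal, categorical time): the estimate at six months is the mean of those still answering minus the baseline mean of everyone. Earlier scores of those who left give no information on their later level.
- *Exchangeable*: earlier scores are used, correctly only so far as the assumed structure fits. A random-intercept mixed model implies the same Vᵢ, so its mean estimates are essentially the same.
- *Correct covariance, by likelihood*: earlier scores are used properly when drop-out depends on them.

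**3. Simulation.** All inputs here are assumptions: four assessments, a true change of -0.50 SD at each follow-up, drop-out without return, and correlation exchangeable (0.5) or AR(1) (0.7). Overstatement = (|estimate| − 0.50) / 0.50.

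*Set A:* 40,000 patients per scenario, about 70-72% retained, drop-out depending on the last observed score with log-odds 0.5 to 1.5 per SD.

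*Set B:* 20,000 patients per scenario, log-odds +0.7 or -0.7 per SD.

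*Set C:* 70% retained, drop-out depending on observed scores, with an added case in which baseline spread is narrowed, as the CES-D entry cut-off may do.

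Estimates at the last visit, about 30% loss, more depressed patients leaving according to the last observed score:

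| Set | Independence GEE | Exchangeable GEE | Likelihood model |
|---|---|---|---|
| A | -0.578 to -0.677 | -0.475 to -0.513 | -0.495 to -0.501 |
| B | -0.605 to -0.618 | -0.483 to -0.510 | -0.497 to -0.507 |
| C | -0.60 to -0.66 | -0.49 to -0.51; narrowed baseline -0.54 to -0.56 | about -0.50 |

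Set A's likelihood model is unstructured. In sets B and C the covariance is the correct one.

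- Independence, set A: 0.078 / 0.50 = 16% to 0.177 / 0.50 = 35%. Set B: 21% to 24%. Set C: 20% to 32%.
- Exchangeable: within about 6% at every follow-up in set A (largest -0.531). In set C with narrowed baseline, 0.04 / 0.50 = 8% to 0.06 / 0.50 = 12%.

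Other conditions, set B:

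- Unselective drop-out: all three methods give -0.50 to -0.52, so differences of 0.02 are simulation noise.
- 15% loss, more depressed leaving: independence -0.546 to -0.561, a bias of about 0.05-0.06 SD.
- 30% loss, less depressed leaving: independence -0.381 to -0.398, an understatement of 20-24%.
- 30% loss, drop-out depending on the current unseen score, more depressed leaving: independence -0.640 to -0.655, exchangeable -0.566 to -0.571, likelihood -0.570 to -0.575. The likelihood model is then biased about as much as exchangeable GEE.

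**The case against.** The strongest reply is that the sentence on GEE is true as written. It says that few patients are lost to the analysis, and GEE does use every available visit. It does not say that drop-out bias is removed. The working correlation, any weights and sensitivity analyses may sit in a full analysis plan that is not shown, and their absence from an article is no fault. With an exchangeable structure the bias is often negligible. All of this stands, and it limits the point. What remains is that the article names a method, gives incomplete data as a reason for it, and a better-protected method is available on the same records.

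A reader might infer that the article expects 30% drop-out related to mood. It does not. The 30% can include patients who stop the course but still answer questionnaires. It can also include controls who "show (spontaneous) remission, are excluded at this point"; these never receive the course and lie outside the GEE population. No section links drop-out to mood, and the direction of bias depends on who leaves.

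A reader might also infer that the randomised comparison is compromised. This point does not show that: the between-group effect is tested by ANOVA and ANCOVA, not GEE.

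**Conclusion.** The point holds as an improvement to one secondary strand of the analysis, not as an error that undermines the trial. Ordinary GEE keeps incomplete records but does not in general guard against drop-out that depends on earlier CES-D scores. If about 30% of scores are missing at six months and more depressed patients leave, a true change of -0.50 SD is overstated by about 20-35% under an independence working correlation (16% at the weakest slope). Under an exchangeable one the bias is negligible to about 10%.

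These sizes rest on an assumed loss, drop-out slope, correlation and true change, none of which the article supplies. The bias is smaller at 15% loss and reverses if improved patients leave. It would be too strong to say that GEE is invalid here, that it will overstate improvement, or that any mixed model cures the problem. A random-intercept model essentially repeats exchangeable GEE, and no method above is protected when drop-out depends on unseen scores.

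**What to change.** In the pre-post paragraph of Statistical Analyses, state the missing-data assumption and replace ordinary GEE with one of these:

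- a likelihood-based repeated-measures model (REML) on all available CES-D scores, with time as categorical and unstructured covariance, not a random intercept alone; or
- GEE with inverse-probability-of-drop-out weights, or after multiple imputation, using earlier CES-D scores in the weight or imputation model.

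Add a sensitivity analysis in which drop-out depends on unseen scores, for example by shifting the imputed values over a stated range in both directions. Robust standard errors are not a substitute: they correct the standard error, not a biased estimate.

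The cost is a change of text and a little more analysis work in standard software, with no extra patients or visits. The unstructured model has more covariance parameters to estimate: 4 × 5 / 2 = 10 for the four CES-D assessments. The randomised ANOVA/ANCOVA comparison is unchanged by this fix.

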## Methods/Design

### Study Design

We chose a two-arm randomised controlled trial (RCT) design; including 286 patients (143/143) (see power calculation). Measurements are scheduled at six points in time in the intervention group: at baseline, directly after completing the web-based intervention, and at 1, 3, 4 and 6 months follow-up. In the control group the same six measurements are scheduled with two additional measurements at 8 and 12 weeks after randomization (see flow chart, Figure 1).

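### The clinical-effectiveness measure (CES-D <16 after the course) is stated as a count with no wait-list comparison, so it cannot separate the course's effect from remission without treatment

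*Protocol article*

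**What the plan says.** The Statistical Analyses section of the protocol article opens with a general rule: "Analyses will be conducted according to the intention to treat principle". It then describes two analyses of the CES-D. The first compares the groups: "ANCOVA's will be performed in order to test whether both groups have different scores on the CES-D, at different points in time". The second has no untreated comparator: "pre-post measurements will be conducted of all participants who have received the intervention", analysed by GEE. Directly after that comes the responder measure: "Clinical effectiveness will be calculated by the amount of people who after completion of the course have a score on the CES-D of <16". No arm, denominator or between-group contrast is attached to it.

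Three other places bear on it:

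- **Study population.** Entry requires a CES-D score of at least 16. Study procedures writes the screening threshold as above 16. On either version nobody enters below 16.
- **Study Design.** The control group has "two additional measurements at 8 and 12 weeks after randomization". Under Control group, the course is offered only after 12 weeks, so both measurements can precede it.
- **Control group.** Wait-list patients are screened again at 12 weeks: "Patients, who do not qualify, i.e. show (spontaneous) remission, are excluded at this point".

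**The concern.** Entry and success are defined on opposite sides of one cut-off on one scale. The screening CES-D is also part of the baseline measurement. Every patient therefore starts as a non-success, and fluctuation around 16, regression to the mean and natural remission can each only add successes. A count taken after the course is the sum of these and of the course's own effect, and nothing in the definition separates them. The protocol's own provision for spontaneous remission shows that the first part is not expected to be zero.

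This is more than missing detail. The sentence says how clinical effectiveness will be calculated, and what it gives is an uncontrolled count. It is the only measure in the article called clinical effectiveness, and the Future implementation section makes dissemination depend on the course proving effective. A reader could easily take the count as evidence of benefit.

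The population is also unclear. If the count follows the preceding sentence and uses everyone who received the course, it mixes two differently selected groups. Intervention patients include those who would have remitted anyway, while treated wait-list patients have had their week-12 remitters removed. The text does not say whether that set is meant.

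**Working it through.** **1. The plan's own figures.** No figure is stated for the <16 measure. The sample size (Power calculation section) reproduces and is not in dispute:

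- n per arm = 2(z₀.₉₅ + z₀.₈₀)² / 0.35² = 2(1.645 + 0.842)² / 0.1225 ≈ 101, against 100 stated. Power with 100 per arm, one-sided 5%, is 79.7%, against 80% stated.
- Inflation: 100 / (1 − 0.30) = 142.9, so 143 per arm and 286 in total, as stated.

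**2. What an inert course would show.** Let q be the proportion of untreated patients below 16 by week 8. The documents give no value, so a range is assumed. With no course effect, the count among 143 intervention patients is 143 × q, and the difference between arms is q − q = 0.

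| Assumed q | Count of 143 | Difference between arms |
|---|---|---|
| 10% | 14 | 0 |
| 20% | 29 | 0 |
| 30% | 43 | 0 |
| 40% | 57 | 0 |

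**3. How much measurement fluctuation alone could add.** Assume applicants' scores at entry and retest are bivariate normal with the same mean m, SD 10 and correlation r, and that entry is selected only on a first score of at least 16. Then

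P(retest <16 | entry ≥16) = [Φ(a) − Φ₂(a, a; r)] / [1 − Φ(a)], with a = (16 − m)/10.

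- m = 20, r = 0.5: (0.3446 − 0.1920) / 0.6554 = 23.3%, about 33 of 143.
- m = 28, r = 0.8: (0.1151 − 0.0665) / 0.8849 = 5.5%, about 8 of 143.

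The mean, SD and correlation are assumptions. Entry also requires a CIDI diagnosis of depression, which this model ignores. That filter probably moves enrolled patients further above 16, so the upper figure is probably too high. True remission would add to either figure.

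**4. The open denominator.** The Power calculation section says: "We anticipate 30% non-completion/exclusion". With 50 successes, chosen for illustration, the rate is 50/100 = 50% if the denominator is the 100 left after that loss, and 50/143 = 35% if it is everyone randomised to the arm.

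**5. Whether a comparator exists.** The course takes 8 weeks and the wait-list completes the questionnaires at 8 weeks, before its own course. A randomised comparison of the <16 proportion is therefore possible on scheduled data. It is just not stated.

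**The case against.** The strongest reply is that this is a loosely worded descriptive measure in a condensed article. It is neither the primary outcome nor a listed secondary one. The test of the course is the ANOVA and ANCOVA on CES-D scores between groups, and the Power calculation section defines the effect size as control against intervention. Natural remission is handled there: an inert course would produce a positive count but no expected difference in the main analysis. This stands and limits the point. A reader might infer that the trial's efficacy conclusion is compromised, and the documents do not support that.

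A reader might also infer that the measure counts only patients who finished the course, so that selective completion inflates it and intention to treat is breached. The text does not fix that. Study Design and Primary outcome measures use completion of the course to name the post-treatment assessment, and the intention-to-treat statement covers the analyses without exception. The 30% is also a combined figure for non-completion and exclusion, not a completion rate. What remains is an ambiguous denominator.

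Finally, denominators and missing-score rules can be left to the full protocol or analysis plan. That is fair, and their absence here is not counted as an error. The missing comparison is different. Intention to treat settles who is analysed, but it does not supply a between-arm contrast for a measure defined as a count after the course.

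**Conclusion.** The point holds for the missing comparison. As stated, the count cannot show the course's clinical effect, because it would be positive for a course that does nothing. Its size cannot be fixed from the documents. The 14 to 57 of 143 rests on assumed untreated rates of 10% to 40%, and the 8 to 33 of 143 from fluctuation alone rests on the distribution assumed in step 3. The direction does not depend on these values: with entry at 16 or above and success below 16, any untreated remission adds to the count.

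The denominator is unclear rather than wrong. The primary CES-D comparison is unaffected. Severity is moderate, and this is a cheap improvement rather than a correction on which the trial's validity depends.

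**What to change.** Redefine clinical effectiveness as the difference between randomised arms in the proportion with CES-D below 16 at the post-treatment assessment, using the week-8 measurement for the wait-list, before controls start the course. Analyse all randomised patients by intention to treat, give a confidence interval, and state in advance how missing scores are handled, with a sensitivity analysis. Counting missing scores as failures should not be the automatic choice, since unequal drop-out between course and wait-list could itself bias the difference. Any count among treated patients can stay as description, with its denominator stated.

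The cost is one reworded sentence and one extra comparison on scheduled measurements. The headline figure will be less favourable, because untreated remission is subtracted. The comparison should be read as an estimate, since the trial was not sized for it. With 100 per arm and a two-sided 5% test, power is about 88% for 40% against 20%, but only about 32% for 40% against 30% (all rates assumed).
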